### **Sample**

**Community selection.** Thirteen pairs of communities participating in the Diffusion study were eligible for inclusion in this study, and 12 pairs have been recruited for the proposed study. These communities have demonstrated their commitment to participate in SDRG research by providing a variety of data for the Diffusion project. In all these pairs, neither community has progressed to the point of installing tested effective policies and programs to address prioritized community risk and protective factors. We have randomly assigned these matched communities to the intervention or control condition. The CTC intervention is expected to produce measurable changes in the prevention service systems in the communities which, in turn, are expected to affect levels of risk, protection, and outcomes among youth aged 9 to 14 over the study period.

The 24 communities in the study were matched with regard to size, poverty and crime indices for the Diffusion project. For the proposed study, this matching maximizes the baseline comparability between the experimental and control communities and reduces potential threats to study's internal validity. Analysis of student survey data from the 1998 and 2000 survey administrations in these communities revealed no significant differences between the intervention and control communities with regard to levels of risk and protective factors or drug use outcomes. Table 2 provides descriptive data on the characteristics of the intervention and control communities

**Including moderate-sized communities.** The communities in the proposed study have a population between 1,500 and 50,000 residents with a clear community identity and boundaries. These are small-to moderate-sized towns with their own governmental, educational and law enforcement structures. Focusing on communities within this restricted size range will limit the generalizability of study findings, but there are important methodological advantages to using towns of this size in community studies (Biglan, 1995). These communities are small enough that their prevention service systems can be clearly defined and measured. Because the enrolled student population in a single grade ranges from 40 to 506 in these communities, with only two communities exceeding 400 students per grade, the study can expose a large proportion of the early adolescent youths in the intervention communities to the chosen programs and policies at a reasonable cost without compromising the power of the experiment. The use of small-to moderate-sized communities increases the likelihood of observing effects of changes in community prevention services on the levels of risk and protective factors experienced by youths in these communities.

**Randomization.** Randomization of one member of each pair of eligible communities occurred prior to recruitment into the proposed study. For each pair, a coin toss determined which of the two matched communities was assigned to the intervention condition.

**Avoiding cross-community contamination.** It is essential to minimize the likelihood of contamination of the control communities, while ensuring that the intervention is fully implemented in intervention communities. Key leaders of control communities will be aware of the project and its requirements,

**Table 2: Baseline Comparisons Between  
Intervention ("I") & Control ("C") Communities**

| Measure                                            | I         | C         |
|----------------------------------------------------|-----------|-----------|
| 2000 Total Population                       | 15,814.25 | 13,927.50 |
| Mean                                               |           |           |
| Standard Deviation                                 | 12,446.06 | 9,824.09  |
| 2000 Percent White                          |           |           |
| Mean Proportion                                    | 88.38%    | 88.74%    |
| 1998 Percent Enrolled in Free/Reduced Lunch | 26.71%    | 33.78%    |
| Mean Proportion                                    |           |           |
| 1998 Percent Unemployed                     | 4%        | 3.09%     |
| Mean Proportion                                    |           |           |
| Implementation Score (All Respondents)      | 1.08      | 1.25      |
| Mean                                               |           |           |
| Standard Deviation                                 | 0.79      | 0.97      |
| Implementation Score (Prevention Leaders)   | 1.58      | 2.08      |
| Mean                                               |           |           |
| Standard Deviation                                 | 0.10      | 0.10      |

| Measure*                      | I     | C     |
|-------------------------------|-------|-------|
| Lifetime Alcohol Use   |       |       |
| Mean Prevalence               | 0.51  | 0.52  |
| 30 Day Alcohol Use     |       |       |
| Mean Prevalence               | 0.27  | 0.28  |
| Lifetime Cigarette Use |       |       |
| Mean Prevalence               | 0.41  | 0.45  |
| 30 Day Cigarette Use   |       |       |
| Mean Prevalence               | 0.14  | 0.17  |
| Lifetime Marijuana Use |       |       |
| Mean Prevalence               | 0.18  | 0.22  |
| Past Year Delinquency  |       |       |
| Mean Prevalence               | 0.21  | 0.23  |
| Total Risk             |       |       |
| Mean                          | -0.03 | 0.01  |
| Standard Deviation            | 0.57  | 0.58  |
| Total Protection       |       |       |
| Mean                          | -0.03 | -0.07 |
| Standard Deviation            | 0.64  | 0.62  |

\*Eighth Grade Students

but will not be oriented to, or provided training in, risk- and protective-focused prevention. They will not receive training or technical assistance in methods for forming a successful community board, conducting a community risk and resource assessment, using epidemiological data to prioritize specific risk and protective factors for preventive intervention, or selecting and implementing tested, effective interventions in mutually reinforcing ways throughout the community. Findings from the current Diffusion project indicate that coherent training and ongoing technical assistance are essential to the successful implementation and institutionalization of risk- and protective-focused prevention as a community-wide prevention strategy.

Risk of contamination will be reduced by the fact that all experimental and control communities are separated by at least 40 miles. In the intervention communities, newspapers, posters, flyers and radio will be the primary media used to educate, recruit and involve local community residents in prevention

activities. These channels are unlikely to contaminate control communities. While some control and intervention communities fall within the same television media markets, the distance between communities will prohibit exposure to the mobilization process and other intervention components used in intervention communities. Exposure to TV alone is unlikely to affect significantly the results of the project. Studies of the impact of mass media interventions to reduce substance use have generally concluded that media interventions alone, without associated community mobilization, policy or programmatic interventions, are not effective at reducing adolescent substance use and related problem behaviors (e.g., Holder & Treno, 1997; Korhonen et al., 1998). Finally, as described later, we will measure the active ingredients of the CTC intervention (community mobilization, implementation of risk- and protective-focused prevention planning, collaboration, and use of evidence-based prevention activities) in both experimental and control communities to identify possible contaminating influences. This will allow any observed contamination to be taken into account in analyses of intervention effects.

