**Figure 1. Study Design**[figure not shown]**Study Design**

The design of the proposed research project is presented in Figure 1, above.

**Community youth samples.** Evaluation of the impact of the CTC intervention on youth outcomes (Aim 1) will include comparisons between the intervention and control communities on trends in risk, protection and drug use and related problem behaviors assessed through repeated cross-sectional surveys of all consenting 6th, 8th, 10th, and 12th grade public school students in each community conducted in 2004, 2006, and 2007 (SS in Figure 1). Comparisons also will be made between the intervention and control communities on individual student-level changes in risk, protection, and initiation of substance use, delinquency, and violence through annual surveys of a longitudinal panel of 200 fourth grade students in each community recruited in the first year of the project and followed throughout the project (Panel in Figure 1).

**Community key informant samples.** Evaluation of CTC's impact on community prevention service systems (Aims 2-4) will include comparisons between the intervention and control communities on measures of collaboration, use of epidemiological data to guide planning and resource allocation decisions, and selection of tested prevention strategies. Data on these measures will be obtained through interviews with key informants in each community conducted in 2004 and 2006 (CKI in Figure 1).

**Community prevention policy and program samples.** Information on the types, quality, and scope of prevention activities consistent with effective interventions for elementary and middle school-aged youths and their families (Aims 3 and 4) will be obtained through structured interviews with prevention service providers and program directors, also conducted in 2004 and 2006 (CRD in Figure 1).

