Student survey administration. Both the cross-sectional and longitudinal surveys will be group administered during one classroom period and will take approximately 45 minutes to complete. The survey items and responses will be read to students in grades 4 and 5 so that reading ability will not be a source of bias. We will make every effort to ensure that subjects are comfortable and to assure them that their responses are confidential. We will further ensure that students do not have the opportunity to see each other's survey forms during administration. Where the students participating in the longitudinal panel constitute a sample rather than the entire grade population of students in study schools, they will be surveyed as a group in a school setting outside of their regular classrooms. As the panel moves into middle school, this procedure will be repeated. Students who move out of the study communities after the second year of the study will be tracked and surveyed individually using similar survey administration procedures and the same self-report, scannable survey instrument. These procedures will maintain parallel survey administration protocols across all participants.

We recognize that surveying students in public schools may underestimate prevalence of problem behavior by missing youths who do not attend school or may bias the estimate by missing students in private schools. However, this need not compromise the internal validity of the study if that bias is the same in both intervention and comparison communities. We will assess this threat in the cross-sectional surveys of 10th and 12th grade students by looking for differences in rates of school dropout in intervention versus control communities. Any differences observed can be addressed in analysis by adding dropout rate as a community-level covariate. Moreover, the longitudinal panel of fourth grade students will be followed regardless of their continued involvement in school.

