One of the major strengths of this study is that multiple years of baseline data are available for each of the communities. This allows us to posit growth models that go beyond describing differences in slopes by taking into account community-level slopes from before the intervention. Thus, the ability of the intervention to produce positive or negative trends within each community can be assessed. Community trends can be taken into account using Bayesian estimates of the baseline slopes and intercepts within each community as covariates when predicting differences in the slope and intercept due to intervention (e.g., Bryk & Raudenbush, 1992). Use of the multiple baseline data points allows us to assess stability, or variance over time, of measures within each community.

These analyses will be extended to address Aim 4 to test the degree to which the use of tested programs in communities affects children's risk and protection exposure and behavior outcomes. The intervention is expected to increase collaboration and the use of effective interventions targeted at priority risk and protective factors. These variables can be used as community-level predictors to test whether they mediate the effect of the intervention on outcomes using the growth modeling approach.

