Given a relationship between these community-level outcomes and student outcomes and an effect of the intervention on student outcomes in Aim 1, these analyses will be further elaborated to examine the CTC framework. Specifically the framework posits that the intervention will positively affect youths through its impact on community prevention service system characteristics such as use of science-based strategies. We propose to examine this aspect of the framework by expanding on the results of the above analyses and testing a mediation model that examines the extent to which the community-level outcomes account for all or most of the effect of treatment on students. This can be examined by entering the community outcomes into the final models from Aim 1 as predictors at the community level. If the intervention is affecting students solely through programmatic effects at the community level, the treatment effect should become zero in this model. This mediation model can then be expanded with a longitudinal model in which community-level outcomes predict changes in student outcomes over the course of the study. These relationships will be examined in both the cross sectional data and in the longitudinal panel. Although theoretically more complex, these analyses are relatively simple expansions of the models used to assess Aim 1.

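### The protocol permits adjusting intervention effects for post-assignment variables: school dropout rate by a stated rule in grades 10 and 12, and contamination measures by leaving their use open

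*Protocol*

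**What the plan says.** **Dropout.** Protocol, Measurement Methods, under Student survey administration, accepts that school surveys miss young people who are not in school. It plans to compare dropout between arms in the grade 10 and 12 cross-sectional surveys, and then says: "Any differences observed can be addressed in analysis by adding dropout rate as a community-level covariate". The panel is followed whether or not its members stay in school.

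**Contamination.** Protocol, Sample, under Avoiding cross-community contamination, says: "we will measure the active ingredients of the CTC intervention (community mobilization, implementation of risk- and protective-focused prevention planning, collaboration, and use of evidence-based". The list closes with preventive work of that kind, and each arm is measured so that contaminating influences can be spotted. The paragraph concludes: "This will allow any observed contamination to be taken into account in analyses of intervention effects". It gives no model and does not say whether the result would be a main or a supporting estimate.

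**Timing.** Randomization preceded recruitment into the study (Sample, Randomization). For collaboration, use of epidemiological data and selection of tested strategies, the Study Design section says: "Data on these measures will be obtained through interviews with key informants in each community conducted in 2004 and 2006".

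**Role of the same measures elsewhere.** Analysis, Aim 1, says: "The intervention is expected to increase collaboration and the use of effective interventions targeted at priority risk and protective factors". It continues: "These variables can be used as community-level predictors to test whether they mediate the effect of the intervention on outcomes". Aim 4 describes what follows when they are entered: "If the intervention is affecting students solely through programmatic effects at the community level, the treatment effect should become zero in this model".

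**Main models.** The effect models written out under Aim 1, including the four-level equations, contain assigned condition, grade, year and pair. None contains a dropout or contamination term.

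**The concern.** Randomization protects a comparison by assigned condition. It does not protect a comparison made at equal values of something that happened afterwards. If the programme changes that variable, adjusting for it takes away the part of the effect that runs through it. If the variable also shares unmeasured causes with the outcome, adjusting adds bias of either sign.

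The dropout rule comes into play only when the arms differ on dropout, which is when adjustment moves the estimate most. A programme effect on dropout is plausible at least for later tenth graders. Every board is expected to choose a school-based intervention, and the tenth graders of Year 5 were in grade 8 in Year 3, when middle-school services start.

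For contamination the risk lies in what is left open. The same measures serve as a way to account for contamination in the effect and as the pathway whose entry is expected to shrink the effect. No sentence keeps the two uses apart. With 24 communities, the choice between an adjusted and an unadjusted estimate could decide the conclusion, and nothing says which one governs.

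**Working it through.** The protocol gives no figure for this point, so there is none to reproduce. The check sets the texts against each other and then illustrates direction and scale.

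**1. Are the variables post-assignment?** Yes. Communities were assigned before recruitment. The key informant and resource data come from 2004 and 2006 (project Years 2 and 4), and dropout is assessed alongside the surveys of Years 2, 4 and 5.

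**2. Do contamination measures and mediators overlap?**

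| Measure | Contamination paragraph | Mediator in Aims 1 and 4 |
|---|---|---|
| Collaboration | yes | yes |
| Use of tested or evidence-based programmes | yes | yes |
| Risk- and protection-focused planning | yes | as a service-system characteristic |
| Mobilization | yes | not named |

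**3. What does a dropout covariate do?** With a linear covariate, adjusted effect = raw difference − b × (dropout rate, intervention − control), where b is the fitted slope. The correction is therefore proportional to the arm difference that triggers it.

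What is wanted is different. Let e be the use rate among enrolled students, d the proportion not enrolled and q the use rate among them. The rate for the whole cohort is (1 − d)e + dq. Including the missing students therefore changes the arm difference by d_I(q_I − e_I) − d_C(q_C − e_C). The slope b carries no information on q, so the covariate does not in general supply this term.

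**4. Can the panel supply q?** No. It starts in grade 4 in Year 1 and is surveyed for five years: 4 + 4 = grade 8. It has no grade 10 or 12 data.

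**5. Illustration of conditioning on a mediator.** The scale is 0.078, the detectable difference for lifetime cigarette use (Table 3, an eighth-grade figure used only as a scale). The implied standard error is 0.078/(t.975 + t.80) = 0.0251 with 10 df and 0.0254 with 11 df; 0.0257 was used. Assumptions not in the protocol: two-sided alpha 0.05, a mediator gap between arms of 1.5 units, SD 0.8 per community, and the mediated shares below. There were 12 pair differences and 4,000 runs per row.

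| Share mediated | Expected after adjustment, −0.078 × (1 − share) | Simulated | Power, unadjusted | Power, adjusted |
|---|---|---|---|---|
| 0% | −0.078 | −0.079 | 0.79 | 0.37 |
| 25% | −0.0585 | −0.059 | 0.78 | 0.22 |
| 50% | −0.039 | −0.041 | 0.76 | 0.13 |
| 75% | −0.0195 | −0.019 | 0.69 | 0.08 |
| 100% | 0 | 0.001 | 0.63 | 0.05 |

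The unadjusted estimate stayed at about −0.078 in every row. The last row is the protocol's own statement in numbers: "the treatment effect should become zero in this model".

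**6. Illustration of a shared cause.** The covariate differs by arm but carries no effect. It shares an unmeasured cause with the outcome (assumed loading 0.5 on each), and the true effect is zero. The fitted slope is 0.5² × 0.0257 × √12 / (0.8 × √2) = 0.0197, so the expected bias is −0.0197 × 1.5 = −0.0295. The simulation gave −0.029, with a rejection rate of 0.09 instead of 0.05. If the cause acts on the two in opposite directions, the sign reverses.

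**The case against.** A reader might infer that the plan adjusts its intervention effects for mediators, so that an effective programme would be reported as ineffective. The protocol does not say this. The contamination paragraph says only what the measurement will allow, and the dropout sentence says what can be done. The specified effect models use assigned condition. Implementation scores are used in analyses distinct from those by condition (Aims 1 to 3), and mediation under Aim 4 follows only after an effect by condition has been found. The statement about the effect becoming zero is conditional on full mediation and describes ordinary mediation analysis. A separate analysis plan could settle how contamination is handled. All of this stands, and it limits the contamination half to a request for a clear boundary.

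The dropout rule is also narrow. It does not touch grade 8, on which power was based, or the panel. Twelfth graders in Year 5 were in grade 9 in Year 2 and grade 10 in Year 3, largely outside the targeted grades, so a programme effect on their dropout is speculative. Selection out of the school survey is a real problem that deserves an answer.

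What does not fall is the rule itself. It is stated, it is triggered by the data, it uses a post-assignment variable, and it does not solve the selection problem it is meant for.

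A reader might also attach a fixed inflation of the standard error, such as ×1.40 or ×1.67 for correlations of .7 or .8 between assignment and these measures. The protocol gives no such correlation, and that arithmetic holds residual variance fixed, so it is not relied on here.

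**Conclusion.** The point holds in a limited form. For dropout, the protocol explicitly permits a covariate adjustment that can bias the grade 10 and 12 effects in either direction and does not in general restore the absent students. For contamination, it leaves open, without prescribing, the entry of measures that overlap its own mediators into the effect estimate.

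The size is not determinable from the protocol. Under a linear model the fraction removed equals the fraction mediated, from none to all. The simulated powers and the bias of about 0.03 depend on the assumed mediator gap, spread and loadings, and show direction rather than expected magnitude. Grade 8 and panel results are unaffected by the dropout rule.

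**What to change.** 1. **Analysis, Aim 1, repeated in the contamination and survey administration paragraphs:** state that the main estimate of the intervention effect is by assigned condition, with pair and pre-intervention covariates only. Models with a time-varying poverty indicator, which Aim 1 also mentions, would then be supporting analyses.
2. **Student survey administration:** replace the dropout-covariate rule with a report of dropout by arm and a sensitivity analysis for grades 10 and 12. That analysis assigns a stated range of use rates to non-enrolled students, separately by arm, using the cohort formula in step 3 of the working. Say that the range is assumed, since the panel ends in grade 8.
3. **Avoiding cross-community contamination:** limit these measures to description, or to the separate implementation and mediation analyses already set out under Aims 1 to 4.

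The cost is wording plus one sensitivity analysis that rests on assumed rates. No new data are needed.
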